## Abstract

**Background:**

Multiple sclerosis (MS) is a complex, chronic and progressive disease and rehabilitation services can provide important support to patients. Few MS rehabilitation programs have been shown to provide health improvements to patients in a cost-effective manner. The objective of this study is to assess the effects in terms of changes measured by a variety of standardized quality of life, mastery, coping, compliance and individual goal-related endpoints. This combination provides the basis for analyzing the complexity of MS and outcomes of a personalized rehabilitation.

**Methods/Design:**

Patients with MS referred to hospital rehabilitation services will be randomized to either early admission (within two months) or usual admission (after an average waiting time of eight months). They will complete a battery of standardized health outcome instruments prior to randomization, and again six and twelve months after randomization, and a battery of goal-related outcome measures at admission and discharge, and again one, six and twelve months after randomization.

**Discussion:**

The results of the study are expected to contribute to further development of MS rehabilitation services and to discussions about the design and content of such services. The results will also provide additional information to health authorities responsible for providing and financing rehabilitation services.

**Trial registration:**

Current Controlled Trials (ISRCTN05245917)

## Background

Multiple Sclerosis (MS) is a complex, chronic and progressive disease with currently more than 10.000 Danes diagnosed [1]. Patient rehabilitation is necessarily also complex, requiring a personalized, multidisciplinary and highly specialized effort [2,3].

Modern immune drug therapy has not convincingly delayed the progressive neurodegenerative process in MS [4] and it remains unclear to what extent medical treatment can prevent permanent loss of functional abilities. Rehabilitation services will thus continue to be as important as pharmacological interventions for patients with MS. As such, they should be designed according to guidelines based on high quality evidence and assessed using standard evaluative methods.

Personalized rehabilitation is based on the premise that every individual is unique in terms of biology, personality, psychology, physical and social ability in combination with a unique life history formed by social circumstances, daily activities and life style. The objective of personalized rehabilitation is to improve patients’ functional status and to improve extroversion, activity and participation by strengthening the individual’s motivation and ability to cope with the disease and related challenges for living an active life and to be active with their own rehabilitation. Personal rehabilitation takes place during meetings between active, well-prepared patients and rehabilitation teams.

MS rehabilitation is a process that from the beginning is matched to the patient's individual needs and desires and includes active involvement of both the patient and relatives. The patient has a personal coach and a trained specialist as sparring partners throughout the rehabilitation process and these provide guidance to the rehabilitation team composed to support the patients’ needs and goals.

Through coaching patient can be supported to set goals for the rehabilitation. Such goals can be two-dimensional: to achieve at positive changes in the person's life and to be realistic about achievable goals for the rehabilitation process. When the goals of the rehabilitation are determined, a unique personalized program may be developed so that the content and intensity match the patients’ needs, opportunities and constraints. The rehabilitation process can therefore be characterized as shared decision-making between the patient (and relatives) and the supervisor and the rehabilitation team with regular assessment of content in the rehabilitation program and progression in relation to results.

The Sclerosis Hospitals at Haslev and Ry were established by the Multiple Sclerosis Society in 1960 to offer specialized treatment to people with MS in Denmark. Since the early 1990s the hospitals have had annual operating agreements with the Danish health authorities and today are highly specialized hospitals with recent quality accreditation from the Danish Quality Model for Hospitals [5].

The Danish Multiple Sclerosis Hospitals provide personalized rehabilitation through a four-week inpatient program after referral by general practitioner or neurologist. A highly qualified and experienced multidisciplinary team collaborates with the patient in assessing and providing a personal program based on the individual patient’s needs. The program includes a range of training, treatment and education focusing both on the whole person and on specific conditions caused by MS. The goal of the rehabilitation program is to improve the patients' functional capacity in all relevant dimensions: participation and activity; physical, social and psychological functioning, including the patients’ ability to cope with the disease and its symptoms and to be active in their own rehabilitation. This personalized rehabilitation program can be seen as a paradigm shift in relation to an earlier and more uniform rehabilitation program.

### Evidence for MS rehabilitation

A recently updated version (April 2011) of a Cochrane review [6] identified ten studies of varying quality and concluded that although MS rehabilitation may have limited effect on body functions, short-term improvement in activity and participation could be observed. Another Cochrane review suggested that exercise therapy might be beneficial for muscle power function, exercise tolerance, mobility-related activities and mood in patients with MS, although no clear effects could be identified in relation to fatigue or perception of handicap [7].

The efficacy and cost-effectiveness of the Sclerosis Hospitals rehabilitation program for MS patients were investigated in a longitudinal study [8], in which participants completed a single outcome instrument (FAMS questionnaire) to measure quality of life at referral, admission, discharge and up to five months after discharge. The study showed an increase in the FAMS score from referral and admission to discharge and thereby identified a statistically significant improvement in quality of life. Although the FAMS scores had decreased five months after discharge, there was still a statistically significant improvement compared with the score at referral. The study had a number of design issues that complicated assessment of the rehabilitation effort. As the study had no control group, part of the observed effect may have been due to factors other than the rehabilitation program. The considerable variation in participants' personal and disease-related factors could also have influenced the observed effects.

### Study objectives

The aim of the planned study is to document the effects of a highly personalized rehabilitation program for MS patients as provided by the Sclerosis hospitals using a randomized controlled study design and standard generic and disease-specific outcome measures. The objective is to assess the program’s effect on patients in terms of changes in disease-specific quality of life and to answer the following questions:

To what extent are the observed effects maintained six and twelve months after discharge?

How do different dimensions of quality of life, functional ability, mastery, coping, compliance and specific measurements of sleep, daily activities, gait, balance and activity limitations correlate?

What individual goals are set before the start of the rehabilitation?

What are the central areas and priorities of the personalized rehabilitation program?

What specific and measurable actions are included in the personalized rehabilitation program?

What effect does the rehabilitation process have on individual patient’s goals and priorities at discharge?

To what extent do patients maintain coping, one month after discharge?

What resource use and costs occur for patients and their relatives, and for the rest of the health care system?

What is the relationship between the obtained effects and costs?

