## Methods and design

The study is designed as a pragmatic clinical trial [9] of a complex intervention with personalized outcomes [10]. It attempts to maximize external validity by incorporating important features of the rehabilitation intervention in real-life settings and allowing individual participant-selected treatment goals and personalized outcomes.

The study design (Figure 1) is a two-hospital controlled trial of the rehabilitation intervention with randomization to either early admission (‘intervention group’; admission within two months after referral and clinical prescreening) or usual admission (‘control group’; admission approximately eight months after referral to the hospital and clinical prescreening). Any differences between these two groups on observed measures between baseline and six-month assessments will be considered as effects of the rehabilitation program. As the control-group patients are admitted to the hospitals after approximately eight months from referral and prescreening, they also contribute with data to the effect of personalized rehabilitation. To observe long-term effects, data collection will be repeated after twelve months.

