### Data collection

The data collection is planned as outlined in Table 1. Measurement times for the early admission group include baseline (Time A1), preparation day (Time A2), day of discharge (Time A3), one-month follow-up after discharge (Time A4), six-month follow-up after baseline (Time A5) and twelve-month follow-up after baseline (Time A6).

**Table 1 T1:** Time points for data collection during the study

	**Intervention (early admission)**	**Control (usual admission)**
Baseline	Time A1	Time B1
6 months after baseline		Time B2
Preparation day	Time A2	Time B3
Day of discharge	Time A3	Time B4
1 months after discharge	Time A4	Time B5
6 months after baseline	Time A5	
12 months after baseline	Time A6	Time B6

Similarly, the six measurement times for the usual admission group are baseline (Time B1), six-month follow-up after baseline (Time B2 - acts as the control measurement – no intervention), the preparation day (Time B3), day of discharge (Time B4), one-month follow-up after discharge (Time B5) and twelve-month follow-up after baseline (Time B6).

Collection of patient-reported outcomes will mainly be based on online versions of the questionnaires, but questionnaires administered at the preparation day and at discharge will be in paper versions (Table 2). Patients who have completed the consent form will be assigned a unique study identification number and a login code to the web-based data collection system SurveyXact (http://www.surveyXact.dk). This password provides access to the questionnaire to be answered in accordance with the measurement time.

**Table 2 T2:** Questionnaires and assessments in the study

**Instruments**	**A1/B1**	**B2**	**A2/B3**	**A3/B4**	**A4/B5**	**A5**	**A6/B6**
	**(baseline)**	**(6 mths after baseline)**	**(preparation day)**	**(day of discharge)**	**(1 mths after discharge)**	**(6 mths after baseline)**	**(12 mths after baseline)**
Personal characteristics							
Initial assessments	x						
Subsequent assessments		x				x	x
Standard outcomes							
MSIS-29	x	x		x		x	x
FAMS	x	x		x	x	x	x
heiQ	x	x			x	x	x
EQ-VAS	x	x		x		x	x
EQ-5D/15D	x	x				x	x
EDSS	x	x				x	x
MFIS	x	x				x	x
ESS/PSQ	x	x				x	x
MYCaW			x	x		x	x
Walking distance test	x	x				x	x
Goal-related outcomes							
Energy-level			x	x		x	x
Cognitive function			x	x		x	x
Physical function			x	x		x	x
Psychological well-being			x	x		x	x
Personal needs			x	x		x	x
Motor and Process Skills			x	x		x	x
Services used during admission							
Use of different services				x			

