## Discussion

This study is designed to investigate the effects of an inpatient rehabilitation program offered to individuals with multiple sclerosis. The results will contribute to further development of MS rehabilitation services and to discussions about the design and content of such service. The results will also provide additional information to health authorities responsible for providing and financing rehabilitation services.

To our knowledge this study will be one of the first randomized clinical trials to examine patient outcomes from a personalized rehabilitation program for MS. A wide variety of outcomes will be assessed immediately after discharge as well as one, six and twelve months after completion of the rehabilitation the program completion. A combination providing the basis for analyzing the complexity of MS and outcomes of a personalized rehabilitation. Cost-effectiveness will be assessed at twelve months.

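### The protocol promises outcomes six and twelve months after discharge, but its six- and twelve-month visits are timed from baseline, so no patient is measured at either point after discharge

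*Protocol article*

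**What the plan says.** Study objectives, first listed question: "To what extent are the observed effects maintained six and twelve months after discharge". The Discussion says outcomes will be assessed "immediately after discharge as well as one, six and twelve months after completion of the rehabilitation".

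The schedule uses another origin. Data collection gives the early group a "six-month follow-up after baseline (Time A5) and twelve-month follow-up after baseline (Time A6". The usual group has a "six-month follow-up after baseline (Time B2 - acts as the control measurement – no intervention", and later a "one-month follow-up after discharge (Time B5) and twelve-month follow-up after baseline (Time B6". Tables 1 and 2 agree. Only the one-month visit (A4/B5) is timed from discharge. The Comparative analysis section uses these same time points and lists nothing later.

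The Abstract (Methods/Design) times the standardized instruments "prior to randomization, and again six and twelve months after randomization" and the goal-related battery at admission, discharge and "again one, six and twelve months after randomization". So it puts the one-month visit on the randomization clock, whereas the goal-related endpoints section and Data collection time it from discharge.

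**The concern.** A question about maintenance is a question about time since treatment ended. The schedule fixes time since baseline, and the wait for admission and the stay itself lie between the two. The wait is the very thing that is randomized, so the gap differs systematically between the groups.

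Two things are at stake. First, the objective and the Discussion give a reader grounds to take the twelve-month visit as twelve months of durability after discharge, which no patient can supply. The protocol's own background shows why this matters: in the earlier uncontrolled study the FAMS score had fallen by five months after discharge. The early group's six-month visit comes before that point. If it were read as six months after discharge, persistence could look better than it is.

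Second, the heiQ line under Comparative analysis compares A1, A4, A5 and A6 with B1, B2, B5 and B6. A6 and B6 share a time since baseline but lie at very different times since rehabilitation.

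**Working it through.** The plan states no time since discharge for these visits, so there is no figure to reproduce. The check is timeline arithmetic.

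**Inputs**
- Early admission: "admission within two months after referral and clinical prescreening" (Methods and design). Usual admission: about eight months after the same origin (same section).
- Preparation day: seven days before admission (Preparation day) and after randomization (goal-related endpoints section).
- Stay: four weeks (Four-week hospitalization), s = 28 / 30.4375 = 0.92 months.
- Baseline: completed before randomization (Abstract).
- Last visit: month 12 after baseline in both groups (Table 1).
- Assumption for the ranges: referral/prescreening and baseline fall at about the same time.

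**Bound that needs no assumption about waiting.** Discharge cannot come sooner than 7 + 28 = 35 days after baseline, which is 35 / 30.4375 = 1.15 months. The last visit is therefore at most 12 − 1.15 = 10.85 months after discharge. Even if the 20 hospital days were taken as 20 calendar days, the bound would be 12 − 27 / 30.4375 = 11.1 months, still short of twelve.

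**Ranges.** With admission at month a, discharge is d = a + 0.92, and a visit at month v falls v − d months after discharge.

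| Group and admission month a | d | Month-6 visit | Month-12 visit |
|---|---|---|---|
| Early, soonest (7 days = 0.23) | 1.15 | A5: 4.85 | A6: 10.85 |
| Early, 1 | 1.92 | A5: 4.08 | A6: 10.08 |
| Early, 2 (limit) | 2.92 | A5: 3.08 | A6: 9.08 |
| Usual, soonest after B2 (6.23) | 7.15 | B2: before admission | B6: 4.85 |
| Usual, 8 | 8.92 | B2: before admission | B6: 3.08 |
| Usual, 10 | 10.92 | B2: before admission | B6: 1.08 |

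So A5 is about 3.1 to 4.8 months and A6 about 9.1 to 10.8 months after discharge (4.85 and 10.85 cut to one decimal). B6 is about 3 months after discharge, and under 5 because B2 precedes the preparation day.

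**Six months after discharge.** A5 and B6 always fall short of it. A6 would meet it only if discharge came at month 6, that is, with admission at 6 − 0.92 = 5.08 months, which neither group's plan provides for.

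**What the question as worded would need.** The visits would fall at d + 6 and d + 12. In the early group that is months 7.15 to 8.92 and 13.15 to 14.92 after baseline; in the usual group, with a = 8, months 14.92 and 20.92. Every twelve-month value lies beyond the last scheduled visit. Time scale ends data collection twelve months after recruitment closes, which does not cover these visits for patients recruited late.

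**Abstract.** One month after randomization would be about 8 − 1 = 7 months before a usual-group patient is admitted, so it cannot be the visit that Table 1 places one month after discharge.

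**The case against.** The best defence is that the operative sections agree with each other. Data collection, both tables and Comparative analysis all run the six- and twelve-month visits from baseline, and the conflict sits in an objective, a Discussion sentence and the abstract. The main comparison, A1 to A5 against B1 to B2, is defined from baseline. The abstract's randomization clock is in practice the same as the baseline clock for those two visits, because baseline is completed just before randomization. All of this stands, and it limits the weight of the point. It does not remove the contradiction: the question and the schedule are both stated outright, and an analysis plan cannot supply a visit the schedule lacks.

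Several stronger readings are tempting but not supported:
- A reader might infer that the main randomized result is compromised. It is not; it does not use time since discharge.
- A reader might infer that the plan commits to reporting A6 as twelve months after discharge. Comparative analysis labels that contrast as baseline against follow-up; the risk of mislabelling comes from the objective and the Discussion.
- A reader might infer that A6 and B6 are pooled or compared throughout. The other long-term contrasts are within group; only the heiQ line sets A6 beside B6.
- A reader might take 3 and 9 months as typical for the early group. They are the lower ends, reached only when admission is at the two-month limit.
- A reader might try to state what share of usual-group patients reach their one-month post-discharge visit only after B6. The protocol gives no spread of waiting times, so that share cannot be derived.

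**Conclusion.** The point holds as an internal inconsistency that should be corrected. The first study question and the Discussion claim follow-up at six and twelve months after discharge that the schedule does not contain. That no patient is measured twelve months after discharge follows from the order of baseline, preparation day and stay alone. The narrower ranges (A5 about 3.1 to 4.8, A6 about 9.1 to 10.8, B6 about 3 and under 5 months) rest on referral and baseline roughly coinciding and on admission going to plan. A baseline later than referral would lengthen the intervals somewhat, but not past the upper limits shown.

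The damage is confined to the maintenance question and to the A6 against B6 part of the heiQ comparison, where about 9 to 11 months since discharge would be set against about 3. The six-month between-group comparison stands as planned.

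**What to change.** 1. Restate the first study question and the Discussion sentence as six and twelve months after baseline. Give the approximate time since discharge for each group: about 3.1 to 4.8 and 9.1 to 10.8 months in the early group, about 3 (under 5) in the usual group. Make no claim of durability at six or twelve months after discharge.
2. Correct the abstract so that the one-month visit is timed from discharge.
3. For the maintenance analyses, heiQ included, use actual months since discharge as the time variable in the random-effects models already planned. Use the post-discharge visits that Table 2 provides for each instrument. Discharge measurements (A3/B4) exist for FAMS, MSIS-29, EQ-VAS, MYCaW and the goal-related measures, but not for heiQ, EQ-5D/15D, EDSS or, as standard outcomes, MFIS and the sleep scales. A model starting at discharge is therefore not available for every outcome.
4. Do not read A6 and B6 as the same time since rehabilitation. On that scale B6 lies closer to A5.

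The cost is wording plus one variable derived from discharge dates, with no added visits. The price is a shorter durability claim: under 11 months in the early group and under 5 in the usual group. Keeping the question as worded would instead require visits beyond month 12 in both groups.

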## Methods and design

The study is designed as a pragmatic clinical trial [9] of a complex intervention with personalized outcomes [10]. It attempts to maximize external validity by incorporating important features of the rehabilitation intervention in real-life settings and allowing individual participant-selected treatment goals and personalized outcomes.

The study design (Figure 1) is a two-hospital controlled trial of the rehabilitation intervention with randomization to either early admission (‘intervention group’; admission within two months after referral and clinical prescreening) or usual admission (‘control group’; admission approximately eight months after referral to the hospital and clinical prescreening). Any differences between these two groups on observed measures between baseline and six-month assessments will be considered as effects of the rehabilitation program. As the control-group patients are admitted to the hospitals after approximately eight months from referral and prescreening, they also contribute with data to the effect of personalized rehabilitation. To observe long-term effects, data collection will be repeated after twelve months.

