### Outcome measures

Patient outcome will be measured by a variety of standardized quality of life (QoL), mastery and individual goal-related endpoints. A combination providing the basis for analyzing the complexity of MS and outcomes of a personalized rehabilitation.

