### Standard endpoints and associated measurement instruments

Disease-specific quality of life: Multiple Sclerosis Impact Scale version 2 (MSIS-29) [24,25] and Functional Assessment of Multiple Sclerosis (FAMS) [16,26]

Mastery: Health Education Impact Questionnaire (heiQ) [27]

Generic Quality of Life: EQ-5D [28-30] and 15D [31]

Expanded Disability Status Scale score (EDSS) [11]

Fatigue: Modified Fatigue Impact Scale (MFIS) ) [32,33] (also used as individual endpoint)

Sleep: Epworth Sleepness Scale (ESS) [34], Pittsburghs Sleep Quality Index (PSQI) [35-38] (also used as individual endpoint)

Self-assessment of the severity of two main self-selected problems for which the patient seeks help and general feeling of well-being (MYCaW) [17,18]

Resource consumption and costs for patients and their relatives, and for the rest of health care service

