### Data analysis

#### Sample size calculation

Determination of the required sample size is based on known data from the previous FAMS study [8,26]. The FAMS total score ranges from 0-170 and the average score at referral was 103 (SD 27). Assuming that a 5% score change indicates a clinically significant change, then the mean score should change to more than 108 i.e. that a clinically significant change requires a 5-point change.

To test a 5-point difference between two groups with 5% statistical significance (alpha) and 90% power (beta), the calculated required number of participants in each group is 613 people. With 80% power the required number of participants is reduced to 458.

If we want to test a 10-point difference, there needs to be 154 people (assuming 90% power) or 115 people (80% power).

The current study participants are expected to be a more homogeneous group than in the previous study, thus the variation in FAMS score is likely to be reduced. If the standard deviation is assumed to be 20 (instead of 27), then 252 patients will be needed in each group to identify a 5% difference with 80% power.

Taking into account correlation between repeated measurements for the same individual and assuming that the correlation between two subsequent measurements is 0.8, a 5-point difference could be identified with 160 participants (90% power) or 120 participants (80% power) in each group.

Based on these assessments a reasonable sample size is considered to be around 200 participants in each of the two groups. The Sclerosis Hospitals expects to admit 1,200 people with multiple sclerosis in the period March 2012 through June 2013. An unknown number will be either excluded from the study or will decline to participate in the study. If an insufficient number of patients has been recruited at the end of the planned inclusion period, a (short) extension of the inclusion period will be possible.

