### Comparative analysis

The following comparative analysis will be conducted:

Difference from Time A1 to Time A5 for intervention group compared with the difference from Time B1 to Time B2 for control group (i.e. difference in outcomes for rehabilitation vs. no rehabilitation at 6-month follow-up)

Difference between Time A1 and Time B1 (i.e. difference between intervention and control group at baseline)

Difference between Time A1 and Times A5 and A6 (i.e. baseline vs. 6- and 12-month follow-up for intervention group)

Difference between Time B3 and Time B6 for control group (i.e. admission vs. 12-month follow-up).

Difference between A2 and A3 for intervention group (pre- vs. post-hospital rehabilitation)

Difference between B3 and B4 for control group (pre- vs. post-hospital rehabilitation).

Difference between Time A1 and Time A4 for intervention group A (baseline vs. one month after hospital rehabilitation)

Difference between Time B3 and Time B5 for control group (pre- vs. one month after hospital rehabilitation)

Changes in Mastery (heiQ) over time: Times A1, A4, A5 and A6 for intervention group compared with Times B1, B2, B5 and B6 for control group

Subgroup analyses will be performed on the individual focus areas, based on data from participants who have completed the goal-related questionnaires.

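### No outcome is named as deciding the six-month comparison, and the design section counts differences on the observed measures generally as programme effects, so the 5% alpha set for FAMS does not cover the conclusion

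*Protocol article*

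**What the plan says.** Five parts of the protocol bear on which outcome carries the conclusion.

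- **Methods and design**, after defining early and usual admission: "Any differences between these two groups on observed measures between baseline and six-month assessments will be considered as effects of the rehabilitation program".
- **Study objectives**: the programme's effect is to be assessed "in terms of changes in disease-specific quality of life", followed by a list of further questions. The Abstract states the objective more widely, across quality of life, mastery, coping, compliance and goal-related endpoints.
- **Outcome measures**: "Patient outcome will be measured by a variety of standardized quality of life (QoL), mastery and individual goal-related endpoints". The list of standard endpoints that follows places MSIS-29 and FAMS together under disease-specific quality of life and does not rank them.
- **Sample size calculation**: "Determination of the required sample size is based on known data from the previous FAMS study". Every figure there refers to the FAMS total, with 5% significance and 80% or 90% power.
- **Comparative analysis**: the main between-arm comparison is "Difference from Time A1 to Time A5 for intervention group compared with the difference from Time B1 to Time B2 for control group", with no outcome named. The only instrument named in that list is heiQ, for a separate analysis over time.

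No outcome is called primary or main anywhere in the document.

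**The concern.** The sections give different answers to the question of what decides the trial: any observed measure, a domain with two scales, or the FAMS total. The first of these is a positive statement and not a silence. An analysis plan that later named one deciding outcome would have to depart from it.

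The 5% alpha and the 80–90% power are worked out for one test of FAMS. If a difference on another scale can equally be reported as the programme's effect, those error rates do not describe the conclusion. The protocol says its results will inform authorities that provide and finance rehabilitation, so what counts as a positive result should be settled before the data are seen.

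**Working it through.** **1. The protocol's own sample sizes.** Two-sided alpha 0.05, equal arms, n per arm = 2(z₀.₉₇₅ + z_power)² SD² / d², where (1.960 + 1.282)² = 10.507 for 90% power and (1.960 + 0.842)² = 7.849 for 80%.

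- d = 5, SD 27: 2 × 10.507 × 729 / 25 = 612.8, so 613; 2 × 7.849 × 729 / 25 = 457.8, so 458.
- d = 10, SD 27: 154 and 115.
- d = 5, SD 20, 80% power: 252.
- d = 5 with correlation 0.8: the stated 160 and 120 are reproduced with SD 27 and a variance factor of (1 + 0.8)/2 − 0.8² = 0.26, that is, the mean of two follow-ups adjusted for one baseline.

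All the stated figures are reproduced, and all are for a single test of the FAMS total.

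**2. How many measures can show a six-month difference.** Table 2 schedules these at A1/B1 and at both A5 and B2: MSIS-29, FAMS, heiQ, EQ-VAS, EQ-5D, 15D, EDSS, MFIS, ESS, PSQI and walking distance. That is 11. Two printed rows each hold two instruments, so counting rows gives 9. MYCaW and the goal-related outcomes have no B2 measurement and are not counted.

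**3. Chance of at least one nominally significant result when nothing differs.** Each measure is tested at two-sided 5%. If the k measures are independent, the chance is 1 − 0.95^k. If every pair has correlation r, with c = 1.96, it is

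1 − ∫ φ(u) [Φ((c − √r·u)/√(1−r)) − Φ((−c − √r·u)/√(1−r))]^k du.

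| Measures able to decide | r = 0 | r = 0.5 | r = 0.7 | r = 0.8 | r = 0.9 |
|---|---|---|---|---|---|
| 2 (FAMS, MSIS-29) | 9.7% | 9.1% | 8.3% | 7.8% | 7.0% |
| 9 (Table 2 rows) | 37.0% | 26.9% | 20.2% | 16.5% | 12.4% |
| 11 (instruments) | 43.1% | 30.4% | 22.3% | 18.0% | 13.1% |

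The protocol gives no correlation between different outcomes. Its 0.8 is between repeated FAMS scores of one patient and cannot be used here, so r from 0 to 0.9 is an assumed range.

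**4. Power of a single FAMS contrast at six months.** With one follow-up adjusted for baseline, the variance factor is 1 − 0.8² = 0.36, so the residual SD is 27 × 0.6 = 16.2.

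- 80% power: 2 × 7.849 × 16.2² / 25 = 164.8, so 165 per arm.
- 90% power: 2 × 10.507 × 16.2² / 25 = 220.6, so 221 per arm.
- At 200 per arm: standard error 16.2 × √(2/200) = 1.62; 5/1.62 = 3.086; 3.086 − 1.960 = 1.126; power 87%, with no drop-out.

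The stated 160 and 120 rest on two follow-up measurements and do not carry over to this contrast.

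**The case against.** The strongest reply is that the Methods and design sentence is about causal attribution. It follows the definition of the two admission times and explains why the six-month comparison isolates the programme: controls have not yet been admitted. It mentions neither significance nor success. That reading is possible. A reader might infer that the protocol declares the programme effective on one significant result among 11, but no such success criterion is written. What remains is that the sentence makes every observed measure eligible, and no other section narrows it.

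A second reply is that FAMS is implied as the lead, since the trial is sized on it and the objective concerns disease-specific quality of life. This narrows the problem but does not close it, because MSIS-29 stands beside FAMS unranked.

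A third reply concerns size. A reader might take 22–43% as the error rate of this trial. The documents do not support that: it needs all 11 instruments to be deciding, a 5% test of each (the 5% appears only in the sample-size section), and correlations no higher than 0.7. The 43% end needs full independence, which is implausible when several scales measure quality of life. This objection stands, and the wider ranges should be reported with their assumptions.

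A reader might also add the lack of blinding to the argument. It affects self-reported scales whether one or eleven decide, and naming FAMS does not cure it.

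Finally, multiplicity adjustment for the remaining measures is ordinary content of an analysis plan, and its absence here is no fault.

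**Conclusion.** The point holds as an inconsistency over what decides the trial. The document ties its alpha and power to FAMS, its objective to a domain with two scales, and its statement about effects to the observed measures generally. Followed as written, the chance of a false claim is above the stated 5% under every reading except one in which FAMS alone decides, and the text never says that. The excess is modest (7–10%) if only the two disease-specific scales can decide, and larger (13–43%, or 12–37% by printed rows) if any scheduled measure can. These sizes depend on the assumed two-sided 5% test per measure, no true effect, and the assumed correlations.

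The documents do point towards FAMS, and the repair is a matter of wording. The point therefore deserves correction but is not of the highest severity.

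**What to change.** In Comparative analysis, name one primary contrast: the between-arm difference in FAMS total at six months (A1 to A5 against B1 to B2), adjusted for the baseline score. FAMS is the natural choice because it is the outcome the trial was sized on. Call all other measures, including MSIS-29, secondary; how they are adjusted or labelled can be left to the analysis plan. Limit the sentence in Methods and design so that the conclusion on effectiveness rests on this contrast.

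In Sample size calculation, state the power for it: about 87% at 200 per arm without drop-out, with 165 per arm needed for 80% and 221 for 90% (SD 27, correlation 0.8, 5 points). The planned size then meets 80% but not 90%.

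The change takes a few sentences, no new data and no change to care. Its cost is that the sponsor gives up claiming success on another scale.
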